#### Secondary outcomes

Secondary outcomes are outlined in Table 1 and include those that evaluate preliminary effectiveness of the decision aid, and those related to feasibility of the trial.

**Table 1 Tab1:** Outline of outcomes, instruments, and data collection

	Instrument Name	Source	Baseline (t_0_)	Post-consult (t_1_)	Follow-up (t_2_)
ENROLMENT					
Eligibility screen			X		
Informed consent			X		
Randomization			X		
INTERVENTIONS					
Decision aid plus surgeon report arm (decision aid, surgeon report, appropriateness checklist)			X		
No decision aid arm (appropriateness checklist)			X		
ASSESSMENTS					
Decision quality * Primary Outcome	Modified version of the HK-DQI	[28]			DQ_2_ [K_0_, Pref_0_, Surg_2_]
Demographics (Birthdate, Sex, Joint)			D_0_		
QoL (Generic)	EQ-5D-5L	[29]	E_0_		E_2_
QoL (Condition-specific)	WOMAC	[31]	W_0_		W_2_
Depression	PHQ-9		P_0_		
Knowledge	Modified version of the HK-DQI	[28]	K_0_		
Decisional conflict	SURE	[32]	DC_0_		
Treatment preference		[4]	Pref_0_		
Preference for involvement in decision-making	CPS	[33]	CPS_0_		
Willingness to have surgery			Will_1_		
Patient-reported shared decision-making	CollaboRATE	[34, 35]		C_1_	
Decisional regret	Decision Regret Scale	[36]			R_2_
Satisfaction		[7]			S_2_
Expectations		[7]			EXP_2_
Surgical consult	EMR			Consult_1_	
Surgery	EMR				Surg_2_
Concordance	HK-DQI	[28]			Con_2_ [Pref_0_, Surg_2_]
Feasibility: Recruitment			Recruit_0_		
Feasibility: Questionnaire Completion			Complete_0_	Complete_1_	Complete_2_

QoL: Quality-of-Life; EQ-5D-5L: EuroQol 5-Dimensions Questionnaire (5-level); PHQ-9: Patient Health Questionnaire; WOMAC: Western Ontario and McMaster Universities Arthritis Index; HK-DQI: Hip and Knee Decision Quality Instrument; CPS: Control Preferences Scale; EMR: Electronic Medical Record

HRQoL will be assessed by the EQ-5D-5L instrument, [27] which is a generic instrument that has been demonstrated to be valid and reliable in arthritis patients, [29] and the condition-specific Western Ontario and McMaster Osteoarthritis Index (WOMAC) instrument. [30] The WOMAC is widely used to evaluate changes in quality-of-life for people with osteoarthritis, and specifically for those undergoing TKA. It includes three subdomains related to pain, stiffness, and physical functioning, and has been shown to be reliable and valid in a variety of patient groups and across a range of interventions. [31] Depression at baseline will be assessed by the Patient Health Questionnaire (PHQ-9). Treatment preference will be elicited based on a question from the appropriateness checklist which asks whether the patient feels the potential benefits of surgery outweigh the potential surgical harms. [4] We will also include the SURE measure of decisional conflict, which includes four additional items that measure personal perceptions of uncertainty in choosing options, factors contributing to uncertainty, and effective decision-making. SURE been shown to be both internally consistent and reliable (test-retest exceeded 0.78), is correlated with the constructs of knowledge, regret and discontinuance, and has the ability to discriminate between those who make and delay decisions. [32] Willingness to have surgery will be assessed using a single item question.

Preference for involvement in decision-making will be assessed by the Control Preferences Scale (CPS) which ranges from “I prefer to make the final treatment decision” to “I prefer to leave all treatment decisions to my doctor.” [33] Patient-reported shared decision-making will be assessed using the CollaboRATE scale, a validated patient-reported measure which measures shared decision making through three brief questions. [33, 34] Decisional regret will be assessed by the 5-item decisional regret scale, [36] and patient satisfaction will be assessed using a validated three-item instrument. [37] In patients who had surgery, we will assess whether the expectations of surgery were met with a question that has been used previously in joint replacement. [7] Lastly, feasibility will be assessed based on recruitment rates, and rate of questionnaire completion pre and post surgery.

### Participant timeline (Fig. 1)

There are three assessments in this trial: baseline (pre-surgical consultation), post-surgical consultation, and follow-up. Since this RCT has been designed to fit within routine practice at the Edmonton Bone and Joint Centre, study specific outcomes will be collected and combined with routine data collection. This will ensure that no data collection is done in duplicate, thereby easing the measurement burden. It will also ensure that the patient decision aid could be integrated into routine practice if proven effective.

#### Baseline assessment (t0)

After completing *Routine Questionnaire 1* (Fig. 1), participants will be screened to determine if they have been scheduled to visit a participating surgeon, and for eligibility in the trial. Eligible participants will be asked for consent to participate in the study, and complete *Study Questionnaire 1* (Fig. 1), either in the decision aid and surgeon report arm or the no decision aid arm. The timing of this assessment will be dependent on when the patient decides to complete the online questionnaire. When the patient attends their surgical consultation, a research assistant will attach a copy of the summary report and appropriateness checklist (decision aid and surgeon report arm) or appropriateness checklist (no decision aid arm) to the patient’s file.

#### Post-consultation assessment (t1)

Following the surgical consultation (approximately 2-weeks post-consult), all participants will be sent an e-mail asking them to complete *Study Questionnaire 2* (Fig. 1) at their convenience. This assessment will ask questions about the surgical consultation and the participant’s involvement in decision-making.

#### Follow-up assessment (t2)

The final follow-up point (3-months post-surgery) will assess a variety of outcomes. For those who had surgery, they will be asked to complete *Routine Questionnaire 3*, while those that did not have surgery will complete *Study Questionnaire 3* at approximately 1 year from baseline (Fig. 1). Both these surveys will assess the patients’ health status (EQ-5D and WOMAC). All participants will then complete *Study Questionnaire 4* (Fig. 1), which assesses patient satisfaction, and some study-specific outcomes including: decisional regret and whether expectations were met. All data collection will be completed through online questionnaires.

### Sample size and recruitment

A previous decision aid trial in hip and knee arthroplasty found that decision quality improved from 44.5 to 56.1% through the use of a patient decision aid and surgeon report. [12] We expect that the current tool will have a greater impact on decision quality through the inclusion of tailored outcome information for each participant based on data from Alberta collected over the past 3 years, rather than presenting average outcome information for all patients. A sample size of 127 participants per arm are needed, to detect an absolute improvement in decision quality of 17.5% (an increase in decision quality from 44.5 to 62%), using a two-sided t-test at the 5% level of significance with 80% power. To account for a 10% loss to follow-up, our target enrolment is 140 patients per arm for a total of sample size of 280. Participants will be recruited from the Edmonton Bone and Joint Centre until the target sample of 280 is achieved. Based on a previous trial run at this centre, [38, 39] we will aim to recruit 40 individuals per month, requiring approximately 7 months to achieve the desired sample size.

### Assignment of interventions

Participants will be randomly assigned to either the decision aid or no decision aid arm in a 1:1 allocation using a computer-generated randomization schedule with permuted blocks of random sizes. The randomization will be conducted in Research Electronic Data Capture (REDCap) software. All participants who meet the inclusion criteria and consent to participate will be randomized.

### Blinding (masking)

It is not possible to blind the surgeons because patients randomized to the decision aid arm will have a summary report in their surgical file (decision aid arm) or not (no decision aid arm). Analysts will be blinded to treatment allocation until after all participants have had their surgeon visits. This will enable some secondary analyses to be performed. At this time point, analysts will not have access to follow-up data.

### Data collection, management, and analysis

#### Data collection methods and data management

Most data collection will be completed electronically and stored on secure servers at the Alberta Bone and Joint Health Institute (ABJHI). Data entry will be facilitated through two platforms: REDCap, and the PROM-based decision aid software. Data will be entered electronically by patients and the appropriateness questionnaire will be completed by surgeons on paper and then entered electronically into the REDCap database by a research assistant. The anonymized data will be stored in a database on a web server that is only accessible to the necessary ABJHI staff and the research project team.

ABJHI has robust controls in place to ensure the security and privacy of identifiable healthcare information; these include physical controls and technological controls. Their security protocols are compliant with requirements set by the University of Calgary, Alberta Health Services, and the Health Insurance Portability and Accountability Act. All electronic identifiable information is secured on ABJHI servers in either folders with permission restricted to the network administrator, or in a relational database with access restricted to the database administrator. Wireless network access is encrypted using secure enterprise WPA2 encryption.

### Statistical methods (Table 2)

The primary analysis evaluating decision quality will be by intention-to-treat. There is no risk of participants in the no decision aid arm receiving the decision aid intervention. However, some participants randomized to the patient decision aid may not complete or engage with the tool in a meaningful way. This includes participants who click through the decision aid without spending sufficient time to read the material. A secondary analysis will assess decision quality while excluding those that do not engage, determined by a minimum of 20 min to complete the decision aid. We will analyze the participants who are lost-to-follow-up using multiple imputation to fully understand the uncertainty due to missing data. Secondary outcomes will be compared as described in Table 2.

**Table 2 Tab2:** Analysis of primary outcome and secondary outcomes

Outcome	Categorical (Cat) Continuous (Con)	Decision aid arm (DA)	No decision aid arm (RP)	Notes
Decision quality	Cat	DQ_2,DA_	DQ_2,RP_	
Quality of Life (Generic)	Con	E_2,DA_ – E_0,DA_	E_2,RP_ – E_0,RP_	
Quality of Life (Condition-specific)	Con	W_2,DA_ – W_0,DA_	W_2,RP_ – W_0,RP_	
Depression	Con	P_2,DA_ – P_0,DA_	P_2,RP_ – P_0,RP_	
Knowledge	Cat	K_0,DA_	K_0,RP_	Modified version of the 5-item HK-DQI
Decisional conflict	Cat	DC_0i,DA_	DC_0i,RP_	Evaluated for each question individually (i = 1–4)
Treatment preference	Cat	Pref_0,DA_	Pref_0,RP_	
Preference for involvement in decision-making	Cat	CPS_0,DA_	CPS_0,RP_	
Willingness to have surgery	Cat	Will_1,DA_	Will_1,RP_	
Patient-reported shared decision-making	Cat Con	C_1,DA_	C_1,RP_	Top-score: complete SDM vs. not complete Mean-score: complete SDM (12) to no SDM (0)
Decisional regret	Con	R_2,DA_	R_2,RP_	
Satisfaction	Con	S_2,DA_	S_2,RP_	Only for those who had surgery
Expectations	Cat	EXP_2,DA_	EXP_2,RP_	Only for those who had surgery
Surgical consult	Cat	Consult_1,DA_	Consult_1,RP_	
Surgery	Cat	Surg_2,DA_	Surg_2,RP_	
Concordance	Cat	Con_2,DA_	Con_2,RP_	
Feasibility: Recruitment	Con	Recruit_0,DA + RP_		Evaluated for the trial and reported as a percentage
Feasibility: Questionnaire Completion	Con	Complete_0,1,2,DA + RP_		Evaluated for the trial and reported as a percentage

HK-DQI: Hip and Knee Decision Quality Instrument; SDM: Shared Decision Making

Categorical outcomes will be compared between groups using Cochran-Mantel-Haenszel chi-squared tests, with the relative difference in proportions between the decision aid and no decision aid arms calculated as relative risks with 95% confidence intervals. If there is imbalance in covariates previously reported to be associated with surgery uptake, such as age or sex, dichotomous outcomes will be assessed using logistic regression and reported as odds ratios with 95% confidence intervals. We will check the usual statistical assumptions and transform continuous data if necessary. We will use SAS software to fit linear models and use generalized linear models where the assumptions and data distributions are not normally distributed.

Analysis of continuous outcomes will be completed with a 2-sample 2-tailed student’s t-test. As with categorical outcomes, if there is imbalance in key covariates, continuous outcomes will be assessed using linear regression, and if the assumptions do not hold, we will use generalized linear models. Feasibility targets are: a) > 70% recruitment of eligible patients completing their PROMs electronically, and b) > 90% of patients completing study questionnaires.

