### No decision aid arm (Fig. 1)

The no decision aid arm will follow routine practice. This includes routine data collection, including several PROMs, but no information on OA, treatment options, or potential outcomes. The only deviations from routine practice include the collection of study-specific questions for informing the effectiveness endpoints and the provision of a printed appropriateness checklist in the patients file by a research assistant in the clinic for completion by the surgeon during the surgical consultation.

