### Outcomes

#### Primary outcome

The primary outcome for this trial is the difference in the proportion of participants making quality decisions between the two arms. Decision quality is determined to be the key outcome for establishing the effectiveness of decision-making interventions, [11] and is defined as “the extent to which patients are informed and receive treatments that reflect their goals and treatment preferences.” [28] A quality decision requires the patient to: a) be knowledgeable, and b) make a decision that is in concordance with their values. [28] Concordance requires that the patients’ values match with the decision that was implemented, defined as whether the patient had surgery or not at the final assessment. To measure knowledge, we modified one question from the 5-item Hip and Knee Decision Quality Instrument (HK-DQI) related to pain when walking after surgery. In the HK-DQI this question reads, “If 100 people have hip/knee replacement surgery, about how many will have less hip/knee pain when walking after the surgery?” Given the overlap with the EQ-5D-5L dimension of pain or discomfort, and that the decision aid provides tailored estimates of outcomes based on clinical and demographic factors, this question was modified to, “If 100 people like you have knee replacement surgery, how many people improve and have NO or SLIGHT pain or discomfort after surgery?” Individuals getting three or more correct responses (out of five) are considered knowledgeable. Concordance will require that the patient’s treatment preference match their chosen treatment. The following question will measure treatment preference: “Do you feel the potential benefits of knee replacement surgery outweigh the potential surgical risks?” Response options include: “yes,” “no,” and “unsure.” Treatment choice will be ascertained through chart review.

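### The 20-minute engagement analysis removes patients from the decision-aid arm only, so it is not a randomised comparison and can be biased in either direction

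*Protocol article*

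**What the plan says.** All of this is in the protocol article.

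- **Primary analysis** (Statistical methods): "The primary analysis evaluating decision quality will be by intention-to-treat".
- **Engagement analysis** (same section): the authors expect that "some participants randomized to the patient decision aid may not complete or engage with the tool in a meaningful way". They therefore add a secondary analysis of the same endpoint, "excluding those that do not engage, determined by a minimum of 20 min to complete the decision aid".
- **Control arm:** Statistical methods states "There is no risk of participants in the no decision aid arm receiving the decision aid intervention". The section on the no decision aid arm says that controls have routine data collection "but no information on OA, treatment options, or potential outcomes".
- **Endpoint** (Primary outcome): a quality decision needs knowledge and concordance between preference and treatment. On knowledge, "Individuals getting three or more correct responses (out of five) are considered knowledgeable". Table 1 places knowledge and preference at baseline, the time point at which the aid is delivered.
- **Adjustment** (Statistical methods): regression is used "If there is imbalance in covariates previously reported to be associated with surgery uptake, such as age or sex".

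**The concern.** Time spent on the aid is behaviour after randomisation, and it is observed in one arm only. Controls who would also have clicked through cannot be identified, so they stay in. The article does not say in words that every control is kept, but it follows: the criterion has no meaning for controls and no substitute is described.

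If time on the aid is related to attentiveness or literacy, it is probably also related to passing the knowledge test, with or without the aid. The retained patients and the controls would then differ before any effect of the tool. The planned adjustment does not repair this. It applies only if there is imbalance, and it is aimed at predictors of surgery uptake, not of engagement.

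This is the only analysis in the article that addresses patients who actually used the tool, and it concerns the primary endpoint. If the intention-to-treat result is null or marginal, it may well be quoted as the effect in users.

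**Working it through.** **Reproducing the plan's figure.** Inputs from Sample size and recruitment: 44.5% versus 62%, two-sided 5%, 80% power. The mean proportion is (0.445 + 0.62)/2 = 0.5325.

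n = [1.96 × √(2 × 0.5325 × 0.4675) + 0.842 × √(0.445 × 0.555 + 0.62 × 0.38)]² / 0.175² ≈ 3.87/0.0306 ≈ 126.4, so 127 per arm, as stated. Target enrolment is 140 per arm.

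**Bias with no true effect.** Let both full arms have 44.5% decision quality. Let e be the share of the decision-aid arm excluded. Let g be the decision quality of would-be engagers minus that of non-engagers, for reasons unrelated to the tool. Then:

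- 0.445 = (1 − e) × p_engaged + e × (p_engaged − g), so p_engaged = 0.445 + e × g.
- Spurious difference = p_engaged − 0.445 = e × g.

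Neither e nor g is in the article; all values below are assumptions. The error rates use a normal approximation with 127(1 − e) retained decision-aid patients against 127 controls.

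| Excluded (e) | Gap (g), points | Spurious difference, points | Relative risk | Two-sided error |
|---|---|---|---|---|
| any | 0 | 0 | 1.00 | 5.0% |
| 20% | 20 | 4.0 | 1.09 | 9.3% |
| 30% | 20 | 6.0 | 1.13 | 14.0% |
| 30% | 30 | 9.0 | 1.20 | 25.5% |
| 40% | 20 | 8.0 | 1.18 | 19.7% |
| 40% | 30 | 12.0 | 1.27 | 38.0% |

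A negative gap reverses the sign: 30% excluded with a gap of −20 gives 0.3 × (−20) = −6 points.

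**Cross-check at 140 per arm.** A null simulation (20,000 runs) gave 9.3%, 15.0% and 27.7% for (20%, 20), (30%, 20) and (30%, 30). The intention-to-treat test rejected in 4.6-4.7% of runs. By hand for (30%, 30): 98 versus 140 patients, pooled rate (98 × 0.535 + 140 × 0.445)/238 = 0.482, SE = √(0.482 × 0.518 × (1/98 + 1/140)) ≈ 0.066. A true mean difference of 0.09 against a critical value of 1.96 × 0.066 ≈ 0.129 gives about 28% rejection. The 40%, 30-point corner was not simulated; its 38.0% comes from the approximation only.

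**The complier estimate and its weak point.** The complier-average effect is the intention-to-treat risk difference divided by (1 − e). With no effect in anyone its numerator is zero on average, whatever g is. Now let the true effect in engaged patients be d, and let patients under 20 minutes gain a fraction f of it:

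- Intention-to-treat difference = (1 − e)d + e × f × d.
- Complier estimate = d × [1 + e × f/(1 − e)].

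With e = 40% and f = 0.5, the intention-to-treat difference is 0.6d + 0.2d = 0.8d, and the estimate is 0.8d/0.6 = 1.33d, an overstatement of one third.

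**The case against.** Four points can fairly be made for the plan.

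1. **Direction.** A reader might infer that the exclusion necessarily favours the aid. The article does not support that. Long completion time may mark slow reading or poor comprehension, and fast readers with good knowledge would be excluded. The gap could be zero or negative. This objection stands.
2. **Size.** A reader might take 4 to 12 points as an estimate. It is not one, because both inputs are assumed. Knowledge is also only one component of the endpoint. If 70% of patients were concordant regardless of engagement (an assumption), a 20-30 point gap in decision quality would need a knowledge gap of 20/0.7 to 30/0.7, about 29 to 43 points. This stands too: the figures are scenarios.
3. **The alternative is not assumption-free.** The complier estimate requires that assignment does nothing for patients under 20 minutes. Someone who reads for 15 minutes has still seen tailored content. The section on the decision aid arm says the surgeon report is generated from what the patient enters in the aid, and the Blinding section says that decision-aid patients will have a report on file. The null simulation could not reveal this, since the assumption holds there by construction. The estimate also adds essentially no new test of no effect beyond intention-to-treat. This stands, and is why a sensitivity range is needed.
4. **Weight.** The analysis is labelled secondary, its threshold is fixed in advance, and the Discussion ties the next study to the primary outcome. This limits the consequences but does not make the comparison a randomised one.

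**Conclusion.** The structural point holds: the rule is explicit, it can act in one arm only, and the stated adjustment does not address the resulting selection. With no true effect the analysis is off by e × g. That is zero if engagement is unrelated to decision quality, 4 to 12 points in favour of the aid for an assumed 20-40% excluded and a 20-30 point gap, and negative if slow completion marks poorer comprehension. For scale, the planned effect is 17.5 points.

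Two stronger readings are not supported: that the bias is known to favour the aid, and that the trial's main conclusion is compromised. The intention-to-treat comparison remains primary and is untouched. The change is worth making because it is cheap and the analysis bears on the primary endpoint.

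**What to change.** - **Make the engagement analysis a complier-average causal effect**, with randomised arm as the instrument: the intention-to-treat risk difference divided by the proportion of all patients randomised to the aid who meet the engagement rule, with a two-stage or bootstrap confidence interval. The article reports relative risks, so the risk difference must be calculated as well. Since controls cannot receive the aid, non-adherence is one-sided.
- **State the assumption** that assignment has no effect in patients under 20 minutes, and add a sensitivity range over f for partial reading or the surgeon report. Without it the estimate is biased upwards whenever those patients also benefit.
- **If the exclusion analysis is kept**, report it beside this one as non-randomised and exploratory. Adjust for baseline predictors of engagement that were recorded before the aid is seen. Knowledge, preference and decisional conflict carry a baseline label in Table 1 but are compared as outcomes in Table 2, so they should not be used as adjusters.

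Cost: one rewritten secondary analysis and no new data. The price is a wider interval and one openly stated assumption.

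### Decisional conflict is compared only item by item; one pre-specified SURE total as the main comparison would be a cheap improvement

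*Protocol article*

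**What the plan says.** The Secondary outcomes section introduces a single instrument: "We will also include the SURE measure of decisional conflict, which includes four additional items that measure personal perceptions of uncertainty". The support it gives is for that instrument: "SURE been shown to be both internally consistent and reliable (test-retest exceeded 0.78), is correlated with the constructs of knowledge, regret and discontinuance", and it adds that SURE "has the ability to discriminate between those who make and delay decisions".

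The Statistical methods section then states that "Secondary outcomes will be compared as described in Table 2". In Table 2, decisional conflict is one row, typed as categorical, with an item index on the outcome symbol and the note "Evaluated for each question individually (i = 1–4". The text below the table says "Categorical outcomes will be compared between groups using Cochran-Mantel-Haenszel chi-squared tests", with relative risks and 95% confidence intervals. Read together, these give four between-arm tests and four relative risks. No total, cut-off, lead item or rule for combining the four is stated.

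Two other multi-item measures are handled differently. Knowledge is reduced to one binary result, three or more of five items correct (Primary outcome section). CollaboRATE has two defined summaries in Table 2: "Top-score: complete SDM vs. not complete Mean-score: complete SDM (12) to no SDM (0".

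**The concern.** The evidence offered for SURE and the quantities to be compared do not line up. Internal consistency, in particular, describes how a set of items behaves together and says nothing about one item alone. The article does not attribute the quoted reliability, correlations and discrimination to single items.

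The practical consequence is that a named outcome has no single result. If one, two or three of the four items differ between arms, the plan does not say whether the aid reduced decisional conflict, and the authors would have to choose a reading after seeing the data. Four chances at a nominally significant result also raise the false-positive risk within this one outcome. That is the lesser point here, because the article states no multiplicity control for any secondary outcome.

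**Working it through.** **The plan's own figure.** The article states no power, level or sample size for decisional conflict. Its only design calculation is for the primary outcome: 44.5% against 62%, two-sided 5%, 80% power, 127 per arm. With the pooled-variance formula for two proportions and a mean proportion of 0.5325:

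n = [1.960 × √(2 × 0.5325 × 0.4675) + 0.842 × √(0.445 × 0.555 + 0.62 × 0.38)]² / 0.175² = 126.4, rounded up to 127.

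The figure reproduces and does not involve SURE, so nothing below bears on it.

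**Inputs for the item-level analysis.** From the article: four items, each compared separately by arm. Assumed: each comparison two-sided at 5%, and a common correlation ρ between the four test statistics. The article gives neither.

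**Chance of at least one false positive, no true effect on any item.**
- Independent items: 1 − 0.95⁴ = 1 − 0.8145 = 0.185.
- Correlated items: simulation of four equicorrelated normal statistics, 1,000,000 draws, counting draws where the largest absolute value exceeds 1.96.

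| Assumed ρ | At least one of four | One summary test |
|---|---|---|
| 0 | 18.5% | 5% |
| 0.3 | about 17.4% | 5% |
| 0.5 | about 15.5% | 5% |
| 0.7 | about 13.0% | 5% |
| 0.9 | about 9.3% | 5% |

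The zero-correlation row fits least well with an instrument described as internally consistent, so the lower rows are the more plausible ones.

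**How clear the answer would be if the aid worked.** Suppose, for illustration, that all four standardised items shift equally, with an expected z of 2 each. Each item then has about 52% power. The variance of a sum of four equicorrelated standardised items is 4 + 12ρ, so the expected z of the total is 8/√(4 + 12ρ). The split column comes from the same kind of simulation with the mean shifted to 2.

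| Assumed ρ | Expected z of total | Power of total | Chance that only one to three items are significant |
|---|---|---|---|
| 0.3 | 2.90 | about 83% | about 72% |
| 0.5 | 2.53 | about 72% | about 60% |
| 0.7 | 2.27 | about 62% | about 46% |

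A split result is therefore likely even when the effect is real and uniform.

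**The opposite case.** At ρ = 0.5 the variance of the sum is 10. If all items shift equally, the total's z is 4/√10 = 1.26 times that of one item. If only one item shifts, it is 1/√10 = 0.32 times. The total gains when the items move together and loses heavily when the effect sits in one of them.

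**The case against.** The strongest reply is that nothing here is contradictory. The article nowhere promises a SURE total or cut-off, and an instrument's internal consistency does not oblige anyone to add up its items. The Secondary outcomes section says that the items cover different things (uncertainty in choosing, what contributes to it, and effective decision-making), so comparing them separately is a coherent, pre-stated choice. Each item gets a relative risk with a confidence interval, and the natural reading of mixed results is which aspects differed. The trial is framed as one of preliminary efficacy. No secondary outcome carries an alpha level or a hierarchy, so treating four items as a family imports a confirmatory frame. The percentages rest on assumed correlations and an assumed level. The total would dilute an effect on one item. The article also gives no SURE response format or scoring rule.

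Most of this stands. A reader might infer that the plan breaks a commitment to a validated score, or that it has a serious multiplicity fault. The article supports neither: it does not call SURE validated (it uses that word for CollaboRATE and the satisfaction instrument), it commits to no total, and it attaches no confirmatory claim to this outcome. Nor is a single score always more efficient, as the one-item case shows.

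Two things survive the reply. The item-level analysis is fixed in Table 2, so this is a stated choice and not a detail left to an analysis plan. And SURE is the only row marked for question-by-question evaluation, with no reason given, although the support cited for it concerns the whole measure.

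**Conclusion.** The point holds as a cheap improvement and not as an error. Decisional conflict is listed as one outcome and supported as one measure, but the plan produces four results and no overall one. The main weakness is this missing single result. Error inflation comes second: 18.5% for independent items and about 9% to 17% at assumed correlations of 0.9 to 0.3, against 5% for one test, all on an assumed 5% level per item. The power and split-result figures are illustrations that rest on an assumed equal shift in every item. The consequence is confined to one secondary outcome.

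**What to change.** In the decisional conflict row of Table 2, pre-specify one between-arm comparison of the total over the four SURE items as the main analysis. Take the scoring from the instrument's source, and change the outcome type and test to match: if the total is treated as continuous, the row is no longer categorical and falls under the t-test that the Statistical methods section gives for continuous outcomes. Keep the four item-level relative risks with 95% confidence intervals as supporting description.

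This needs no new data and no change to procedures, only an edit to one row, made before outcome data are compared by arm. The costs are that item-level findings become supportive only, and that an effect limited to one item would show weakly in the total. Retaining the item-level estimates leaves such an effect visible.
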